## Abstract

**Background:**

High-dose influenza vaccines provide better protection against influenza infection than standard-dose in persons aged 65 years and above; however, in most countries, high-dose vaccines are not widely implemented. Assessing the relative effectiveness of high-dose compared to standard-dose vaccines on hospitalizations and mortality would enable more robust public health and cost-effectiveness estimates. This study aims to investigate the feasibility of conducting a pragmatic randomized clinical trial in Denmark comparing high-dose to standard-dose vaccines utilizing existing vaccination infrastructure and the Danish nationwide health registries for data collection.

**Methods:**

The DANFLU-1 trial (NCT05048589) is a pragmatic, open-label, active-controlled randomized trial randomizing Danish citizens aged 65–79 years to either high-dose quadrivalent influenza vaccine or standard-dose quadrivalent influenza vaccine. The study utilizes the infrastructure of a private vaccination provider (Danske Lægers Vaccinations Service) for recruitment, inclusion, randomization, and vaccination. All collection of baseline and follow-up data including safety monitoring is performed centrally by the Department of Cardiology at Herlev and Gentofte Hospital, Copenhagen, Denmark using the Danish nationwide health registries. The study aims to include 40,000 participants during the 2021/2022 influenza season. The primary endpoints address feasibility and include the number of participants enrolled, randomization balance, and representativeness compared to the Danish general population. Relative vaccine effectiveness will also be assessed, however, this feasibility study is not powered for clinical outcomes and may be affected by the COVID-19 pandemic.

**Discussion:**

The DANFLU-1 study is investigating the feasibility of conducting a large-scale pragmatic clinical trial in Denmark utilizing existing infrastructure and the Danish nationwide registries. This will provide valuable insight, especially for potential future fully powered vaccine trials, but also for trials wishing to investigate other interventions.

**Trial registration:**

Clinicaltrials.gov: NCT05048589, registered September 17, 2021.

## Background

Influenza is a contagious, acute viral respiratory illness that may affect all age groups with presentations ranging from mild upper respiratory symptoms to severe cases resulting in hospitalization and/or death. In the northern and southern hemispheres, influenza causes seasonal epidemics of disease almost every winter. In tropical regions, influenza circulates continuously throughout the year, causing outbreaks more irregularly [1]. Global estimates of influenza-associated mortality and morbidity indicate that influenza causes approx. 290,000–650,000 respiratory deaths and approx. 5 million hospitalizations for lower respiratory tract infection annually [2, 3]. The elderly (aged 65 and above) and individuals with chronic healthcare conditions such as heart disease, lung disease, or diabetes display a heightened risk of influenza complications compared to younger healthy adults [4, 5]. Vaccination is the most effective method for reducing the incidence of influenza and influenza-related morbidity and mortality [6]. Seasonal vaccination of persons aged 65+ and other high risk groups is strongly recommended by the European Centre for Disease Control and numerous national governmental immunization guidelines; in the USA, the Centers for Disease Control and Prevention additionally recommends vaccination for all persons aged ≥ 6 months without contraindications [4, 5].

Previous studies have shown that antibody response and protection elicited by the standard formulation influenza vaccine are reduced for individuals aged 65 years or older as compared to younger adults [7, 8]. A high-dose (HD) influenza vaccine formulation (Fluzone® High-Dose), containing 60 μg of antigen from each influenza strain included in the vaccine, has been shown in a US randomized controlled trial (RCT) to reduce the incidence of influenza by approx. 25% with no increase in serious adverse events compared to standard-dose (SD) vaccine formulations in persons aged 65+ [9]. Observational studies have also demonstrated better effectiveness of the HD influenza vaccine across multiple influenza seasons, in different populations, and in different settings versus SD influenza vaccines [10]. A recent cluster-randomized trial also found that the HD vaccine reduced respiratory-related hospital admissions in nursing home residents aged 65+ when compared to SD vaccines [11].

A quadrivalent formulation of the HD influenza vaccine (QIV-HD; Fluzone® High-Dose Quadrivalent; Efluelda®) was licensed for use in persons aged 65+ in Denmark in April 2020. In the Danish 2020/2021 influenza season, a trivalent HD vaccine was offered to citizens aged 85+ only, and in the 2021/2022 influenza season, the Danish government vaccination program has been expanded to offer QIV-HD vaccine to citizens aged 80 years or older (age limit changed to 82 years after the protocol was finalized). Therefore, in the 2021/2022 season, citizens aged 65–79 years are offered SD vaccines despite evidence indicating that the licensed HD vaccine could reduce morbidity and improve clinical outcomes in this population group. To date, no individually randomized studies have assessed the effect of HD vs SD influenza vaccine on the incidence of hospitalizations for influenza or pneumonia and mortality. There would be significant public health interest in quantifying the potential benefit of QIV-HD vs SD quadrivalent influenza vaccine (QIV-SD) with respect to clinically important and impactful outcomes such as hospitalization for influenza or pneumonia in the 65–79 age group, including as inputs for cost-effectiveness analyses to guide future vaccination policies.

RCTs serve as the gold standard for decision-making, but they are complex, costly, and their results can sometimes be difficult to generalize to real-world patient populations due to restrictive inclusion/exclusion criteria. However, nationwide healthcare databases provide the opportunity to combine the gold standard of individual randomization—thereby providing unbiased results from which causal conclusions can be inferred—with representative real-world patient populations and pragmatic data collection [12]. With this approach, rigorous randomization of treatment allocation is integrated with existing data-collection platforms which may be used to collect baseline and follow-up information, greatly reducing complexity and costs. In Denmark, nationwide administrative registries enable effective collection of such information for all persons residing in Denmark [13, 14]. This is highly desirable in studies comparing one vaccine to another since these studies involve the estimation of relatively small effect sizes as compared to placebo-controlled studies, therefore requiring large sample sizes.

### Purpose

This pragmatic pilot RCT was designed to test the feasibility of randomizing a representative sample of Danish citizens aged 65–79 years to QIV-HD or QIV-SD in the 2021/2022 influenza season in a registry-based setting utilizing existing vaccination infrastructure to inform the planning of future large-scale, fully powered RCTs.

## Study design and methods

### Design and organization

The study is a pragmatic, registry-based, open-label, active-controlled randomized trial serving as a pilot trial for a potential future fully powered trial. The study aims to randomize (1:1) 40,000 Danish citizens aged 65–79 years to QIV-HD or QIV-SD in the 2021/2022 influenza season (Fig. 1, Table 1).

**Fig. 1 Fig1:**
[figure not shown]
Study flowchart. *DLVS* Danske Lægers Vaccinations Service, *QIV*-*HD* high-dose quadrivalent influenza vaccine, *QIV*-*SD* standard-dose quadrivalent influenza vaccine

**Table 1 Tab1:** SPIRIT figure

Timepoint	Enrolment	Allocation and vaccine administration	Post-allocation	Close-out
	***Prior to or on Day 0***	***Day 0***	***3 months after vaccination***	***May 31, 2022***
**Enrolment**				
**Eligibility screen**	X			
**Informed consent**	X			
**Allocation**		X		
**Interventions**				
***QIV-HD***		X		
***QIV-SD***		X		
**Assessments**				
***Registry-based safety assessment***			X	
***Registry-based endpoint assessment***				X

*QIV*-*HD* high-dose quadrivalent influenza vaccine, *QIV*-*SD* standard-dose quadrivalent influenza vaccine

The study is conducted as a collaboration between (1) the Cardiovascular Non-Invasive Imaging Research Laboratory (CIRL) at the Department of Cardiology, Copenhagen University Hospital–Herlev and Gentofte, Copenhagen, Denmark; (2) the private vaccination provider Danske Lægers Vaccinations Service (DLVS); and (3) Statens Serum Institut (SSI). CIRL acts as the central trial coordination site and is responsible for study oversight, safety monitoring, and processing and analyzing registry data including endpoints. DLVS has over 20 years of experience in organizing vaccination sessions at both pop-up sites and stationary clinics and is responsible for recruitment, inclusion, randomization, vaccination, and initial data collection. The vaccination sessions are geographically dispersed across Denmark and participants are included at upwards of 1000 different vaccination sessions. SSI provides access to vaccination and microbiology databases and contributes expert knowledge on influenza vaccination.

Participants are randomized 1:1 to either QIV-HD or QIV-SD. Randomization is performed centrally using a computer-generated block randomization scheme.

The study aims to integrate a pragmatic randomized trial into routine vaccination practice by requiring only one study visit and performing registry-based follow-up without the need for additional visits or contacts with the study sites.

### Study population and sample size

Due to the pragmatic nature of the study, the only inclusion criteria are that the participants are aged 65–79 years and that the informed consent form has been signed and dated. The only exclusion criterion is allergy/hypersensibility toward the vaccines used in the study. Potential contraindications (fever etc.) are evaluated as part of routine practice on the day of vaccination.

Potential participants will be recruited by sending invitation letters to citizens vaccinated in prior seasons as recorded in an existing DLVS database. In addition, broader website-based advertising is also utilized. The projected sample size of 40,000 was chosen to, in the opinion of the study team, place vaccine delivery and vaccination program infrastructure and systems under sufficient pressure to inform the feasibility and planning of a future fully powered study. A preliminary sample size calculation yielded a required study population of 208,675 participants for a fully powered study under the assumptions of a true relative vaccine effectiveness (rVE) of QIV-HD to QIV-SD of 15%, an overall attack rate of hospitalization for influenza and/or pneumonia of 0.86% in the QIV-SD group, alpha of 0.05, and power of 0.90. Thus, this present study is not powered for the assessment of any clinical endpoints.

### Vaccines

The QIV-HD vaccine (Fluzone® High-Dose Quadrivalent, Sanofi Pasteur) contains 60 mg of hemagglutinin (HA) antigen for each of the four strains included in the vaccine. For this pragmatic study, any approved QIV-SD vaccine can be used as the active comparator. Both vaccines contain the same 4 strains based on the recommendations of the World Health Organization for the 2021/2022 northern hemisphere influenza season.

### Data collection and data sources

Initial data collection is performed by DLVS, who registers the social security number and name of the subject, the signed informed consent, randomization allocation, and the name and batch number of the administered vaccine. The informed consent form is electronic with signatures written on a tablet. All initial data including the electronic informed consent are automatically transferred to a central study database administered by CIRL.

The Danish health system is publicly funded and renowned for its administrative registries recording clinical events. The registries are frequently used for observational research [15]. In collaboration with the Danish Health Data Authority, the social security numbers of each subject are used to link the study database to the Danish nationwide administrative health registries. The Danish National Patient Registry contains information on all in- and outpatient visits in the Danish public health system [13]. The Danish National Prescription Registry contains claimed prescriptions at all pharmacies in Denmark [16]. The Danish Civil Registration System contains information on date of birth, deaths, immigration, and emigration [14]. The Danish Registry of Causes of death can be used to retrieve specific causes of death [17]. All vaccinations including prior influenza vaccinations can be retrieved from the Danish Vaccination Register [18]. The Danish Microbiology Database contains results from routinely performed tests including influenza [19]. Several registries containing socioeconomic data including personal income, pension, unemployment, and sickness benefits enable accurate assessment of the sociodemographic characteristics of the study population [20]. Education status can be retrieved from the Population Education Register [21].

Utilizing information from the registries enables the central trial coordination site to easily obtain information on baseline comorbidities, medication use at baseline, demographics, and socioeconomics as well as monitor clinical events during follow-up for safety assessment and clinical endpoints. The classification codes and definitions (e.g., ICD-10 and ATC codes) used for baseline conditions, medication use at baseline, and clinical endpoints are prespecified and can be found in Tables 2, 3, and 4. Prespecified definitions of registry-collected events ensure a minimum of bias in the assessment of these variables.

**Table 2 Tab2:** Prespecified definitions for baseline conditions

Condition	ICD-10/ATC codes	Diagnosis type	Inpatient/outpatient/minimum required length of stay/other criteria	Timeframe
Chronic obstructive pulmonary disease	J42-J44	A or B	Any	≤ 10 years prior to randomization
Asthma	J45	A or B	Any	≤ 10 years prior to randomization
Chronic lung disease	A15-A16, D860, E84, J42-J47, J84, Z942	A or B	Any	≤ 10 years prior to randomization
Diabetes (ICD-10)	E10-E14	A or B	Any	≤ 10 years prior to randomization
Diabetes (ATC)	A10	–	≥ 1 claimed prescription	≤ 180 days prior to randomization
Hypertension (ICD-10)	I10-I15	A or B	Any	≤ 10 years prior to randomization
Hypertension (ATC)	Diuretics: C03 β-blockers: C07 Calcium blockers: C08 Renin-angiotensin system inhibitors: C09	–	≥ 1 claimed prescription from ≥ 2 drug classes	≤ 180 days prior to randomization
Dyslipidemia (ATC)	C10	–	≥ 1 claimed prescription	≤ 180 days prior to randomization
Ischemic heart disease	I20-I25	A or B	Any	≤ 10 years prior to randomization
Myocardial infarction	I21	A or B	Any	≤ 10 years prior to randomization
Heart failure	I50	A or B	Any	≤ 10 years prior to randomization
Other cardiomyopathy	I42-I43	A or B	Any	≤ 10 years prior to randomization
Atrial fibrillation	I48	A or B	Any	≤ 10 years prior to randomization
Other arrhythmia	I44-I47, I49	A or B	Any	≤ 10 years prior to randomization
Valvular disease	I34-I37	A or B	Any	≤ 10 years prior to randomization
Pericarditis	I30-I31	A or B	Any	≤ 10 years prior to randomization
Endocarditis	I33, I38-I39	A or B	Any	≤ 10 years prior to randomization
Myocarditis	I40-I41	A or B	Any	≤ 10 years prior to randomization
Pulmonary heart disease	I26-I28	A or B	Any	≤ 10 years prior to randomization
Cerebrovascular disease	I60-I69	A or B	Any	≤ 10 years prior to randomization
Peripheral vascular disease	I70, I74	A or B	Any	≤ 10 years prior to randomization
Congenital heart disease	Q20-Q26	A or B	Any	≤ 10 years prior to randomization
Chronic cardiovascular disease	I20-I28, I34-I37, I42-I50, I60-I69, I70, I74, Q20-Q26	A or B	Any	≤ 10 years prior to randomization
Cancer	C00-C97 (not C44)	A or B	Any	≤ 10 years prior to randomization
Chronic kidney disease	E102, E112, E132, E142, I120, N02-N08, N11-N12, N14, N18-N19, N26, N158-N160, N162-N164, N168, M300, M313, M319, M321B, Q612-Q613, Q615, Q619, T858-T859, Z992	A or B	Any	≤ 10 years prior to randomization
Liver disease	B15-B19, K70-K77, C22, I982, Z944, D684C, Q618	A or B	Any	≤ 10 years prior to randomization
Immunodeficiency (ICD-10)	B20-B24, D80-D84, D89, O987, Z21, Z940-Z944, Z948A	A or B	Any	≤ 10 years prior to randomization
Immunodeficiency (ATC)	H02AB, L04	–	≥ 1 claimed prescription	≤ 180 days prior to randomization
Neurological/neuromuscular disease	F00-F03, G10-G14, G20-G23, G30-G32, G35-G37, G40-G41, G70-G73, G80-G83, G91-G95	A or B	Any	≤ 10 years prior to randomization
Dementia	F00-F03, G30, G311-G312,	A or B	Any	≤ 10 years prior to randomization
Rheumatic disease	M05-M06, M32-M34, M353	A or B	Any	≤ 10 years prior to randomization

All baseline conditions are defined from ICD-10 codes except for diabetes, hypertension, dyslipidemia, and immunodeficiency, where ATC codes are also used. *ICD* International Classification of Diseases, *ATC* anatomic therapeutic chemical

**Table 3 Tab3:** Prespecified definitions for medication use at baseline

Medication	ATC codes	Number of prescriptions	Timeframe
Antithrombotics	B01	≥ 1 claimed prescription	≤ 180 days prior to randomization
Renin-angiotensin system inhibitor	C09	≥ 1 claimed prescription	≤ 180 days prior to randomization
Calcium blockers	C08	≥ 1 claimed prescription	≤ 180 days prior to randomization
Beta blockers	C07	≥ 1 claimed prescription	≤ 180 days prior to randomization
Diuretics	C03	≥ 1 claimed prescription	≤ 180 days prior to randomization
Aspirin	B01AC06	≥ 1 claimed prescription	≤ 180 days prior to randomization
Statins	C10AA	≥ 1 claimed prescription	≤ 180 days prior to randomization
Inhaled beta-2 agonists	R03A	≥ 1 claimed prescription	≤ 180 days prior to randomization
Inhaled anticholinergics	R03BB, R03AL01-07	≥ 1 claimed prescription	≤ 180 days prior to randomization
Inhaled glucocorticoids	R03BA, R03AK, R03AL08-09, R03AL11-12	≥ 1 claimed prescription	≤ 180 days prior to randomization
Insulin	A10A	≥ 1 claimed prescription	≤ 180 days prior to randomization
Non-insulin antidiabetic medication	A10B	≥ 1 claimed prescription	≤ 180 days prior to randomization
Systemic glucocorticoids	H02AB	≥ 1 claimed prescription	≤ 180 days prior to randomization
Immunosuppres-sants	L04	≥ 1 claimed prescription	≤ 180 days prior to randomization

Medication use at baseline will be assessed using ATC codes. *ATC* anatomic therapeutical chemical

**Table 4 Tab4:** Prespecified definitions for clinical endpoints

Endpoint	ICD-10 codes	Diagnosis type	Inpatient/outpatient/minimum required length of stay/other criteria	Timeframe
Influenza and/or pneumonia hospitalization	J09-J18	A	Inpatient, at least 1 night	≥ 14 days after vaccination and up to May 31, 2022
Respiratory disease hospitalization	J00-J06, J09-J18, J20-J22, J40-J47, J80-J81, J85-J86, J96	A	Inpatient, at least 1 night	≥ 14 days after vaccination and up to May 31, 2022
Cardiovascular disease hospitalization	I11, I13, I20-I25, I30-I31, I33, I38-I42, I46-I50, I60-I69, I74	A	Inpatient, at least 1 night	≥ 14 days after vaccination and up to May 31, 2022
Cardio-respiratory disease hospitalization	I11, I13, I20-I25, I30-I31, I33, I38-I42, I46-I50, I60-I69, I74, J00-J06, J09-J18, J20-J22, J40-J47, J80-J81, J85-J86, J96	A	Inpatient, at least 1 night	≥ 14 days after vaccination and up to May 31, 2022
Any hospitalization	Any	Any	Inpatient, at least 1 night	≥ 14 days after vaccination and up to May 31, 2022
COVID-19 hospitalization	B342, B972	A	Inpatient, at least 1 night	≥ 14 days after vaccination and up to May 31, 2022
All-cause death	–	–	–	≥ 14 days after vaccination and up to May 31, 2022

All clinical endpoints are defined from ICD-10 codes. *ICD* International Classification of Diseases

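### Two prespecified ATC rules under-count users of fixed-dose combinations: some R03AL inhalers are missing from the anticholinergic row, and single-code antihypertensive combinations score as one class

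*Protocol article*

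**What the plan says.** The section on data collection and data sources states that the code definitions for baseline conditions and medication are fixed in advance in Tables 2 and 3.

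- **Table 2, hypertension by ATC.** The classes are "Diuretics: C03 β-blockers: C07 Calcium blockers: C08 Renin-angiotensin system inhibitors: C09", and the criterion is "≥ 1 claimed prescription from ≥ 2 drug classes" in the 180 days before randomization. No rule covers one product that contains two of these classes.
- **Table 2, hypertension by ICD-10.** A separate row takes I10-I15, diagnosis type A or B, any contact, up to 10 years back. The table footnote says that conditions rest on ICD-10 codes "except for diabetes, hypertension, dyslipidemia, and immunodeficiency, where ATC codes are also used". The ATC route is therefore an addition to the ICD-10 route.
- **Table 3, inhaled anticholinergics:** "R03BB, R03AL01-07".
- **Table 3, inhaled glucocorticoids:** "R03BA, R03AK, R03AL08-09, R03AL11-12".
- **Table 3, inhaled beta-2 agonists:** the whole of R03A, which includes every R03AK and R03AL code.
- **Table 3, diuretics and calcium blockers:** C03 and C08 respectively, with nothing from the combination codes under C07 or C09.

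The abstract names randomization balance and representativeness among the primary feasibility endpoints. The outcomes section lists baseline characteristics by arm and against the general population aged 65-79 years.

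**The concern.** A dispensed combination product carries one ATC code. Under a prefix rule it can reach only the classes whose prefix it matches, whatever it contains. Two participants on the same substances can then be classified differently because one takes a single tablet and the other takes two.

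For inhalers, Table 3 already uses multi-row counting: R03AL01-07 count as both beta-2 agonist and anticholinergic. The later R03AL codes break that pattern, because they are left out of the anticholinergic row.

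At stake is the accuracy of a few descriptive rows: hypertension, diuretics, calcium blockers and inhaled anticholinergics. They matter here because the baseline description is itself an outcome. The section on assessment of success also names the reliability of registry-derived baseline characteristics as part of the overall evaluation that informs a fully powered trial.

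**Working it through.** The plan states no figure that depends on these rules, so there is none to reproduce. The check applies the listed prefixes literally to individual codes.

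**Inputs.** The prefixes and the two-class criterion come from Tables 2 and 3. What the codes contain is not in the document. It is taken as an assumption from the ATC classification that the plan adopts: R03AL combines adrenergics with anticholinergics, and C07, C08 and C09 include products that contain a second listed class.

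**Step 1, Table 3 inhaler rows.**

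| Code claimed | Beta-2 agonist | Anticholinergic | Glucocorticoid |
|---|---|---|---|
| R03AK | yes | no | yes |
| R03AL01-07 | yes | yes | no |
| R03AL08, 09, 11, 12 | yes | **no** | yes |
| R03AL10 | yes | **no** | no |

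A participant with any R03AL08-12 claim still enters the anticholinergic row if there is also an R03BB or R03AL01-07 claim in the same 180 days. The gap concerns those without one.

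**Step 2, Table 2 hypertension rule.** Count the distinct prefixes among C03, C07, C08 and C09; at least 2 are required.

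| Claims in 180 days | Classes counted | Hypertension by ATC |
|---|---|---|
| C09DA01 alone (renin-angiotensin inhibitor plus diuretic) | 1 | no |
| C09DB01 alone (renin-angiotensin inhibitor plus calcium blocker) | 1 | no |
| C07BB02 alone (beta blocker plus diuretic) | 1 | no |
| C03AA01 and C09CA01, separate tablets | 2 | yes |
| C08CA01 and C09DA01 | 2 | yes |
| C07AB02 and C09DA01 | 2 | yes |

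The first and fourth lines show the inconsistency: a diuretic and a renin-angiotensin inhibitor fail in one tablet and pass in two. The last two lines show that a further listed class restores the classification. An I10-I15 diagnosis within 10 years does so as well, whatever the claims.

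**Step 3, Table 3 antihypertensive rows.** C09BA02 and C09DA01 match only the renin-angiotensin row, so the diuretic is not counted. C09BB02 and C09DB01 also match only that row, so the calcium blocker is not counted. C07BB02 and C07FB02 match only the beta-blocker row. ICD-10 codes cannot recover any of these, because medication rows use claims alone.

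**Step 4, size.** For drug-defined hypertension, in percentage points:

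undercount = (share on two or more classes) × (share of those who have them only as one combination code)

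The document gives neither factor. Purely as assumptions, 25-35% and 10-25% would give 0.25 × 0.10 = 2.5 points up to 0.35 × 0.25 = 8.75, about 8.8 points, before ICD-10 diagnoses recover some. For anticholinergics, an assumed use of 5-8% with an assumed 15-35% having only R03AL08-12 would give 0.05 × 0.15 = 0.75, about 0.8 points, up to 0.08 × 0.35 = 2.8 points. These ranges show how the size depends on the inputs. They are not estimates for this population.

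**The case against.** The strongest reply is that the tables contain more safeguards than a quick reading suggests, and that several larger conclusions do not follow. Most of this stands.

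- **A reader might infer that every combination product is filed under one class.** Table 3 shows otherwise. Because the beta-2 agonist row takes all of R03A, listed inhaler combinations are counted in two rows; only R03AL10 falls in one.
- **A reader might infer that all users of combined antihypertensives are scored as not hypertensive.** The ICD-10 row and any second listed class recover some of them. Only those with neither are missed.
- **A reader might infer that triple-inhaler users, and with them severe lung disease, drop out of the description.** They remain in the beta-2 agonist row and, for codes 08-09 and 11-12, the glucocorticoid row. Chronic obstructive pulmonary disease, asthma and chronic lung disease are defined by ICD-10 in Table 2 and are unaffected.
- **A reader might infer bias between arms.** The same codes apply to both arms and are fixed beforehand, so randomization leaves no mechanism for systematic imbalance.
- **A reader might infer a demonstrated bias in representativeness.** An assumed 5-point difference in combination-only share at 35% prevalence would give 0.05 × 0.35 = 1.75 points, against a half-width of 1.96 × √(0.35 × 0.65 / 40,000) = 0.47 points. Nothing in the document suggests such a difference, and the sum ignores ICD-10 recovery. It cannot serve as evidence.

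It can also be said that reporting by ATC group is an accepted convention, since "Medication use at baseline will be assessed using ATC codes", and that product contents lie outside the document. The convention would explain the C03 and C08 rows. It does not explain why one R03AL branch counts as anticholinergic for codes 01-07 and not for 08-12. Nor does it suit a rule that uses the number of classes as a marker of disease.

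**Conclusion.** The point holds in a narrow form. Followed exactly, the plan omits from the anticholinergic row any participant whose only such claim is R03AL08-12. It scores as not hypertensive any participant treated only with a single-code two-class product who has no other listed class and no I10-I15 diagnosis. The diuretic and calcium-blocker rows miss the same products.

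The consequence is understated prevalence in a few baseline rows, of a size that cannot be computed from the document. The comparison with the general population is distorted only if combination prescribing differs between participants and population. That comparison is assumed to use the same code lists on both sides. No rVE estimate, clinical endpoint or sample size is touched, and no numerical success criterion depends on these rows.

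The conclusion rests on literal prefix matching and on the ATC contents stated as assumptions above. The impact is modest. A correction is still worthwhile, because representativeness is a primary feasibility endpoint and the tables present these definitions as final.

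**What to change.** Amend the code lists in Tables 2 and 3:

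- Define inhaled anticholinergics as R03BB plus all of R03AL, and keep R03AL08-09 and R03AL11-12 under glucocorticoids as well.
- Count each C07, C08 and C09 combination code towards every listed class it contains, both in the two-class hypertension rule and in the Table 3 rows for diuretics, calcium blockers, beta blockers and renin-angiotensin inhibitors.
- State that the identical mapping is used for the general population comparison.

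The cost is a short code-list edit and a few lines of programming. The prescription registry is already a data source and its ATC codes are already in use, so no new data are needed. If tables have already been produced, reporting the affected rows under both definitions would show how much the change matters.

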### Outcomes

All outcomes are assessed using data collected from the Danish administrative health registries. The outcomes are primarily feasibility-oriented and include:Number of persons contacted by recruitment letterNumber of participants included and randomized to QIV-HD or QIV-SDAgreement between randomization group and administered vaccineAssessment of baseline characteristics according to randomization groupComparison of baseline characteristics between study population and Danish general population aged 65-79 years on October 1, 2021

The study is not powered for assessing clinical endpoints. However, for feasibility assessment purposes, event rates and relative vaccine effectiveness (rVE) will be assessed for the following clinical outcomes:Hospitalization for influenza and/or pneumoniaHospitalization for any respiratory diseaseHospitalization for any cardio-respiratory diseaseHospitalization for any cardiovascular diseaseHospitalization from any causeAll-cause mortalityHospitalization for COVID-19

The clinical outcomes are specified further in Table 4. rVE will be calculated as:

rVE = (1-(C_HD_ /N_HD_)/(C_SD_/N_SD_)) × 100%

Where:

C_HD_: describes the number of endpoints occurring in the QIV-HD arm meeting the endpoint definition

N_HD_: describes the number of participants in the QIV-HD arm

C_SD_: describes the number of endpoints occurring in the QIV-SD arm meeting the endpoint definition

N_SD_: describes the number of participants in the QIV-SD arm

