### Statistical analysis

Purely descriptive outcomes such as number of persons contacted and recruited will be presented in raw numbers. The proportion of the number of participants recruited compared to the number of persons contacted will be calculated and presented along with a 95% confidence interval. The proportion of participants not receiving the correct intervention will be calculated for each randomization arm and presented along with 95% confidence intervals. In the comparison of baseline characteristics between the study population and the overall Danish general population aged 65–79 years, characteristics will be compared using methods appropriate for each characteristic. Continuous baseline variables will be summarized using means and standard deviations or medians and interquartile ranges. Binary or categorical variables will be compared using frequencies and proportions. Event rates for clinical endpoints will be presented as attack rates and incidence rates with 95% confidence intervals. rVE estimates will be presented along with 95% confidence intervals. *P* values < 0.05 will be considered statistically significant. rVE estimates will be considered statistically significant if the confidence interval does not include 0.

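### Clinical endpoint windows open 14 days after vaccination but rVE divides by everyone in the arm, so a randomized, unvaccinated participant counts in N and can never be a case (minor)

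*Protocol article*

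**What the plan says.** - **Window.** Each of the seven rows of Table 4 has the timeframe of at least "14 days after vaccination and up to May 31, 2022". The last row, "All-cause death", has the same lag as the six hospitalization rows.
- **Numerator.** In the rVE formula under Outcomes, C_HD "describes the number of endpoints occurring in the QIV-HD arm meeting the endpoint definition", so the Table 4 window applies to it.
- **Denominator.** N_HD "describes the number of participants in the QIV-HD arm" and N_SD "describes the number of participants in the QIV-SD arm". Neither is limited to people who were vaccinated or alive at day 14.
- **Meaning of arm.** Statistical analysis uses the term for the randomized group and foresees departures within it: "The proportion of participants not receiving the correct intervention will be calculated for each randomization arm".
- **Timing.** Table 1 has one Day 0 column, "Allocation and vaccine administration". Study population and sample size adds: "Potential contraindications (fever etc.) are evaluated as part of routine practice on the day of vaccination".
- **Other time frames.** The baseline look-backs in Tables 2 and 3 all run back from randomization.

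**The concern.** Vaccination happens after randomization, and in this trial the allocation is open. A window that opens only on vaccination makes eligibility to be a case depend on a post-randomization event, while the denominator does not. If more people go unvaccinated in one arm, that arm loses potential cases but keeps its N, and so looks better protected.

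Separately, an outcome called all-cause mortality omits the deaths closest to the intervention.

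The clinical results are unpowered, but the event rates and rVE are collected to judge feasibility, and the same definitions could be carried into a fully powered trial.

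**Working it through.** **Inputs from the article (Study population and sample size; Design and organization).** QIV-SD attack rate 0.86%, true rVE 15%, and 40,000 participants at 1:1, so 20,000 per arm. The article gives no figure for the unvaccinated share, so a range is assumed. Its preliminary size of 208,675 for a full trial is not in dispute here. With these inputs and two-sided alpha of 0.05 (sidedness is not stated), power at that size is 0.91 against the stated 0.90.

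**Step 1, formula.** Let u be the share of an arm that is randomized but not vaccinated. Assume the vaccinated in the two arms have the same underlying risk. Cases come only from the vaccinated, while N is everyone:

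rVE_obs = 1 − (1 − rVE) × (1 − u_HD)/(1 − u_SD)

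**Step 2, results.**

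| u_HD / u_SD | Factor | True rVE 0% reads | True rVE 15% reads |
|---|---|---|---|
| 1% / 1% | 1.000 | 0.0% | 15.0% |
| 2% / 1% | 0.98/0.99 = 0.990 | 1.0% | 15.9% |
| 1% / 2% | 0.99/0.98 = 1.010 | −1.0% | 14.1% |
| 5% / 1% | 0.95/0.99 = 0.960 | 4.0% | 18.4% |
| 1% / 5% | 0.99/0.95 = 1.042 | −4.2% | 11.4% |

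The shift per one-point difference is about 1 point at a true rVE of 0% and about 0.9 point at 15%. The sign follows whichever arm has more unvaccinated people.

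**Step 3, attack rate.** Even with equal shares, the reported QIV-SD rate falls: 0.86% × 0.99 = 0.851% at u = 1%, and 0.86% × 0.95 = 0.817% at u = 5%.

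**Step 4, early deaths and rVE.** People who die in days 0–13 enter the same factor. With assumed early-death shares of 0.10% (HD) and 0.05% (SD), the hospitalization rVE is 1 − 0.85 × 0.9990/0.9995 = 15.04%, a shift of less than 0.1 point.

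**Step 5, early deaths and the mortality rate.** The article gives no vaccination dates, so October 1 to November 30 is assumed. Follow-up to May 31 is then 242 to 182 days. Under a constant hazard the omitted share of deaths is 14/242 = 5.8% to 14/182 = 7.7%.

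**Step 6, scale.** At 20,000 per arm the expected cases are 172 (SD) and 146.2 (HD). The standard error of the log risk ratio is √(0.9914/172 + 0.99269/146.2) = 0.112. The 95% interval around an rVE of 15% is about −5.9% to 31.8%.

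**The case against.** The case against giving this much weight is strong, and most of it stands.

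- **Few people are likely to be affected.** Allocation and vaccination share Day 0. The sentence on contraindications does not say that the check follows randomization, and no text describes refusal after allocation or later vaccination. The planned report on incorrect intervention covers people given the wrong vaccine, who do have a window. It leaves room for people given none but does not show that there will be any.
- **Early deaths kept in N are not a bias.** Dividing by everyone in the arm preserves the randomized comparison, and Step 4 shows how little moves. A common lag in both arms is a reasonable design choice for hospitalization.
- **Early deaths are not lost.** Under Safety monitoring, deaths and hospitalizations are assessed about three months after vaccination, and the Discussion confirms that they are collected.
- **Rules on analysis sets may be elsewhere.** An article often leaves them to the full protocol or the analysis plan.

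A reader might infer that the as-randomized comparison is lost, or that the rule favours QIV-HD. The documents support neither. They give no unvaccinated share, no difference between arms and no direction for one.

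What survives is narrower. The article itself fixes both the window and the denominator, and together they leave a randomized, unvaccinated person in N with no way to be counted in C.

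**Conclusion.** The point holds as a minor one. The stated window and denominator do not match for anyone randomized but not vaccinated. The effect on rVE is zero when non-vaccination is balanced and about 0.9 to 1 point per one-point imbalance, in either direction. This rests on assumed shares and on equal underlying risk among the vaccinated. Against an interval of roughly −6% to 32%, such a shift would not alter how this trial is read, and Assessment of success sets no rVE threshold for moving on.

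The mortality outcome omits about 6–8% of deaths under the assumptions in Step 5. That affects the reported rate and the outcome's name. It should not be read as a material bias in rVE or as deaths going unseen.

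**What to change.** 1. In all seven rows of Table 4, count the 14-day lag from randomization instead of vaccination, and state that N is all randomized participants in the arm. Tables 2 and 3 already use randomization as their anchor. Where vaccination is on Day 0 as planned, the dates do not change.
2. Report all-cause mortality from randomization (day 0) beside the lagged version, and label each.

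People who die in days 0–13 would still be in N for the six hospitalization outcomes. That is acceptable, because the same rule then applies to every randomized participant in both arms.

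**Cost.** A wording change in Table 4 and one extra mortality analysis. If early deaths are unaffected by the vaccine, the day-0 mortality rVE is diluted by about 6–8% of its value. For illustration, a lagged 15% would read 15 × (1 − 0.058) = 14.1% to 15 × (1 − 0.077) = 13.8%.
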